### 2.8 Study Outcome measures: Clinical Outcomes

The following clinical outcomes (see Table 2 for definitions) will be evaluated: 1) Transfusion Requirements (red cells, platelets and plasma), 2) Transplant Related Mortality, 3) Maximum grade of acute Graft versus Host Disease [14] 4) Veno-occlusive Disease [15], 5) Serious Infections [16], 6) Bearman Toxicity Score [17], 7) Bleeding [18], 8) Quality of Life [19,20], 9) Number of Hospitalizations and 10) Number of ICU Admissions. Further, we will document any transfusion reactions and the duration of storage of each red cell unit prior to infusion.

**Table 2 T2:** Definitions and Description of Clinical Outcomes

*Transfusion Requirements*	This defined as the number of transfusions received by the recipient between the 1^st ^day of Stem cell reinfusion (Day 0) and Day 100 post Hematopoietic Stem Cell Transplantation.
***Transplant Related Mortality***	This is defined as the incidence of death from any cause at 100 days post Hematopoietic Stem Cell Transplantation.

***Maximum grade of acute Graft versus Host Disease (GVHD)***	The incidence of acute GVHD up to Day 100 will be compared. Acute GVHD will be graded according to the Przepiorka Criteria [14].

***Serious Infection***	Clinically important infections will be ascertained using Centre for Disease Control criteria [16]. Infections will include: serious infections such as nosocomial pneumonia; deep tissue infections (peritonitis, mediastinitis) and bacteremia from organisms not considered normal skin flora, and judged important enough to treat by the attending team. All grade 4 and 5 infections (according to the Common Terminology for Adverse Events v.4) will be recorded in the Data Collection Forms. In addition, the following information will also be recorded in the Data Collection Forms: Type of organism (bacterial, viral, fungal or protozoal) (suspected or documented).

***Bearman Toxicity Score***	This is a validated scoring system [17] to assess toxicity during HSCT. In this system, grade I toxicity is reversible without treatment and grade 2 is not life threatening, but requires treatment. Grade 3 requires life-support intervention and grade 4 is fatal. Regimen-related toxicity in each organ system was scored as the highest grade achieved in that organ system through day 28, except that deaths occurring after day 28 as a result of regimen-related toxicity occurring before day 28 are also scored as grade 4. Adverse events that could be attributed to infection (culture-documented), bleeding or other medications are not scored as regimen-related toxicity. The maximum toxicity is the highest grade recorded in any individual organ system and the cumulative toxicity score is the sum of the highest grades recorded for all eightorgan systems.

***Veno-Occlusive Disease***	Diagnosis requires 2 of 3 criteria, occurring within 20 days of transplantation: 1) Bilirubin > 34.2 μmol/L (2 mg/dL), 2) Hepatomegaly or RUQ pain of liver origin and 3) > 2% weight gain due to fluid accumulation [15].

***Bleeding***	The WHO Scale [18] is a credible, standardized and validated scale to assess bleeding. Grade 3 and 4 bleeding will be recorded in the data collection forms.

***Quality of Life***	Both the FACT-BMT [20] and EQ-5D [19] scales will be used to document quality of life. The FACT consists of 5 subscales that measure physical well-being, functional well-being, social/family well-being and emotional well-being. The BMT subscale of the FACT includes additional items specifically designed to test quality of life and symptoms specific to BMT patients. EQ-5D is a standardized measure of health status developed by the EuroQol Group in order to provide a simple, generic measure of health for clinical and economic appraisal.

HSCT: Hematopoietic Stem Cell Transplantation

### 2.9 Blinding

This is an open labeled study. It will be impossible to blind the assigned red cell transfusion trigger to participants and bedside caregivers since the standard of care requires daily knowledge of hemoglobin concentration as part of the participants' overall HSCT care and safety. There will be no specific measures to blind research coordinators and study statisticians, as the clinical outcomes sought as listed in Section 2.8 are "hard" clinical outcomes and assigned primarily by the bedside caregiver. Consequently, the risk of measurement bias is minimal.

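### Section 2.9 calls every clinical outcome hard and measurement bias minimal, but among the Section 2.8 outcomes only all-cause death clearly fits that description

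*Protocol article*

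**What the plan says.** Section 2.9 states that the trial is open label and gives a reason tied to daily hemoglobin monitoring: "It will be impossible to blind the assigned red cell transfusion trigger to participants and bedside caregivers". It then adds: "There will be no specific measures to blind research coordinators and study statisticians". The justification is that "the clinical outcomes sought as listed in Section 2.8 are 'hard' clinical outcomes and assigned primarily by the bedside caregiver", and the section closes: "Consequently, the risk of measurement bias is minimal".

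Section 2.8 and its Table 2 define the outcomes this covers. Mortality is death from any cause at day 100. Other entries read differently:

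- Quality of life: "Both the FACT-BMT [20] and EQ-5D [19] scales will be used to document quality of life".
- Serious infection includes events "judged important enough to treat by the attending team".
- Veno-occlusive disease (VOD) needs two of three criteria, one of which is "Hepatomegaly or RUQ pain of liver origin".
- Bearman toxicity: "Adverse events that could be attributed to infection (culture-documented), bleeding or other medications are not scored as regimen-related toxicity".
- Acute GVHD and bleeding are graded on clinical scales. Hospital and ICU admissions are counted.

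Section 2.16 compares all of these between arms, each with a significance test and a 95% confidence interval. Sections 2.2, 2.7 and 2.11 say the pilot will help define a feasible primary endpoint for the definitive trial, define its sample size and estimate event rates.

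**The concern.** Both reasons given for minimal bias are weak. The first, that the outcomes are hard, does not fit the definitions in Table 2. The second, that the bedside caregiver assigns them, offers no protection when that caregiver knows the arm and often directs the care that produces the outcome.

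What is at stake is how the pilot's results are read. Told that measurement bias is minimal, a reader has no reason to treat a difference in quality of life or toxicity score more cautiously than a difference in deaths. If such a difference came from expectation or from unequal recording, it could be taken for a signal when the definitive trial is planned. The statement also serves as the reason for leaving the analyst unmasked, which is one of the few protections an open-label trial can still have.

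**Working it through.** **Outcome definitions against the Section 2.9 claim**

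| Outcome (Section 2.8, Table 2) | Who determines it | Clearly hard? |
|---|---|---|
| Death from any cause, day 100 | Fact of death | Yes |
| Transfusion counts | Record count, but giving a transfusion is a care decision, and transfusion outside the trigger is allowed (Section 2.3) | As to measurement only |
| Quality of life | Unblinded patient, possibly at home (Table 3 footnote) | No |
| Serious infection | Partly the attending team's decision to treat | No, though Section 2.16 analyses only grades 4 and 5 |
| Bearman score | Grade plus attribution of cause | Partly: grade 3 needs life support, grade 4 is fatal |
| VOD | Two of three criteria | Partly: bilirubin is a laboratory value and weight is measured, though its cause must be judged |
| Acute GVHD grade | Clinical grading | No |
| Bleeding | WHO grade, only grades 3 and 4 recorded | Partly |
| Hospital and ICU admission | Care decision | No, as to cause; the count itself is factual |

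For VOD, pain or hepatomegaly cannot make the diagnosis alone, but it can decide the case when only one other criterion is met. A note to Table 3 adds a further route for bias: patients who have been discharged are presumed free of transplant toxicity. Discharge is decided by unblinded staff, so recorded toxicity could differ between arms if discharge timing does.

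**The plan's own figure.** The point disputes none. The nearest is the 7.3% power in Section 2.11 (15% versus 10%, 50 per arm, two-sided alpha 0.05). A continuity-corrected normal approximation gives 6.5% and Fisher's exact test 6.1%, both close to it; the uncorrected approximation gives 11.4%. That figure concerns mortality, which this point does not touch.

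**How large could a bias be?** The documents give no size, so the bias values below are assumptions. The input n = 50 per arm is from Section 2.11; the p < 0.01 cut point and two-sided testing are from Section 2.16.

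*Reclassified events.* One patient in an arm: 1/50 = 2 points. Two patients: 2/50 = 4 points.

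*Unequal ascertainment, no true effect.* Spurious difference = true rate × difference in detection.
- True rate 20%, detection 90% versus 80%: 0.20 × 0.10 = 2 points.
- True rate 40%, detection 90% versus 70%: 0.40 × 0.20 = 8 points.

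Sampling error, for comparison: at 30% in both arms, the 95% half-width is 1.96 × √(2 × 0.30 × 0.70 / 50) = 18 points.

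*Quality of life, no true effect.* Standard error of a standardised difference = √(2/50) = 0.20 SD, so the 95% half-width is 1.96 × 0.20 = 0.39 SD. The chance of a significant result is about Φ(shift/0.20 − critical value).

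| Assumed shift | p < 0.05 (1.96) | p < 0.01 (2.576) |
|---|---|---|
| 0.2 SD | Φ(1.0 − 1.96) = 17% | Φ(1.0 − 2.576) = 6% |
| 0.3 SD | Φ(1.5 − 1.96) = 32% | Φ(1.5 − 2.576) = 14% |
| 0.5 SD | Φ(2.5 − 1.96) = 71% | Φ(2.5 − 2.576) = 47% |

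The stricter cut point makes a false signal less frequent, but it does not remove the bias from the estimate or from its confidence interval.

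**The case against.** The strongest reply has four parts.

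First, the pilot's primary goal is feasibility, and Section 2.16 calls secondary endpoints exploratory and uses p < 0.01. A reader might infer from this point that the definitive endpoint will be chosen from biased arm differences. The protocol does not say so: Sections 2.2 and 2.11 speak of feasible endpoints and event rates. This stands, and the consequence is therefore only that a biased difference could mislead.

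Second, several outcomes have firm anchors: bilirubin for VOD, life support or death for the upper Bearman grades, culture-documented infection as a Bearman exclusion, and only grade 3 and 4 bleeding. This also stands. It narrows the room for bias in those outcomes but does nothing for quality of life or for decisions to treat and admit.

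Third, the caregiver clause can be read as saying only that masking coordinators and statisticians would add little when someone else assigns the outcomes. That reading is fair for the clause, but it does not support the conclusion that bias is minimal.

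Fourth, rules for missing data and outliers may be in an analysis plan that is not shown. That stands, so their absence is no part of this point. The decision to leave statisticians unmasked is different, because Section 2.9 states it.

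It is also tempting to set a 2 to 4 point reclassification against the 5-point mortality difference assumed in Section 2.11. That compares unlike things, since death from any cause cannot be regraded. Sampling error is the proper yardstick, and a shift of 2 to 4 points, or even 8, lies well inside it.

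**Conclusion.** The statement in Section 2.9 is wrong as written. The label fits day-100 all-cause death without qualification and transfusion counts as to measurement only. Quality of life is fully exposed to open-label reporting. The judged outcomes and both kinds of admission are exposed to varying degrees.

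The comparison of the main clinical outcome is unaffected. Open-label delivery is justified in the text and is not at fault. A reader might infer that the pilot's results are shown to be biased, but the documents give neither the size nor the direction of any bias. For event outcomes, the assumed distortions of 2 to 8 points are small beside a sampling half-width of about 18 points at a 30% rate. For quality of life, an assumed shift of 0.2 SD is about half the 95% half-width; shifts of 0.3 to 0.5 SD would produce false signals often, even at p < 0.01. The calculations rest on these assumed shifts, on complete data from 50 patients per arm, and on a normal approximation.

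The correction is worth making because it changes what the pilot can claim for these outcomes, and it costs little.

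**What to change.** 1. In Section 2.9, restrict the hard-outcome and minimal-bias statement to death from any cause, and to transfusion counts as regards measurement only.
2. State that between-arm differences in quality of life, serious infection, VOD, acute GVHD grade, Bearman score, bleeding grade, and hospital and ICU admission are open to open-label bias. Add that they will not by themselves be used to choose or size the definitive primary endpoint. Pooled event rates and data completeness may still be used for that.
3. Replace the statement that statisticians will not be masked: the analyst works with coded arms until data-handling decisions are final, and hemoglobin and red-cell data, which reveal the arm, are released last.

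Cost: wording, and a coded dataset from the Methods Centre. No extra assessor or visit is needed. The hemoglobin and red-cell analyses are slightly delayed. Section 2.15 has the study statistician summarise interim reports that include the pre-transfusion hemoglobin difference, so someone other than the final analyst would need to prepare that item, or the masking would be partial. Coding the arms protects only the analysis; it does not remove patient or caregiver bias, which is why the second item is needed.

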### 2.10 Screening, Baseline and Follow-up assessments

Potential participants will be identified by screening at HSCT transplant consultation and/or planning visits. Following written informed consent, demographic information will be collected and participants will be screened for eligibility at the screening visit (see Table 3 for study schedule and procedures at all study visits).

**Table 3 T3:** Schedule and Evaluation of Outcomes

		Study Entry	Scheduled Assessments (± 3 days as inpatient; ± 5 days as outpatient)					
			Day 0	Day 7	Day 14	Day 28	Day 60	Day 100
Demographics/Baseline characteristics	Trial Case Number	x						
	Date of Birth	x						
	Gender	x						
	Indication for HSCT	x						
	Stem cell Source	x						
	CD34 cell count	x						
	Donor Type (allos only)	x						
	HLA compatibility (allos only)	x						
	ABO blood type	x						
	ABO compatibility (allos only)	x						
	CMV compatibility (allos only)	x						
	Karnofsky Functional Scale	x						
	Conditioning regimen	x						
	HCT-CI	x						
	CBC	x	all available values					
Quality of Life Scales	EQ-5D and FACT-BMT†	x		x	x	x	x	x
Transfusion Assessments	Red Cells Transfusion Assessment		As needed					
	Platelets Transfusion Assessment		As needed					
	Plasma and Cryoprecipitate Transfusion Assessment		As needed					
Transplant Assessments	Bleeding Assessment				x	x		x
	Infection Assessment				x	x		x
	VOD Assessment^#^					x		
	Bearman Toxicity Assessment^					x		
	aGVHD*							x
	Admission to ICU		As needed					
	Hospital Admission		As needed					
	Mortality Assessment							x

NB Scheduled Assessments will be required even if the patient is discharged; the assumption is that no transplant toxicities have occurred if the patient is discharged

† Quality of Life Scales may be completed at home to be mailed or handed in

^# ^Presence/Absence within the 1st 21 days of HSCT (by Seattle Criteria) ^ Highest grade to be completed * Highest grade of aGVHD to be completed

HLA: Human Leukocyte Antigen; CMV: Cytomegalovirus; HCT-CI: Hematopoietic Cell Transplantation-Comorbidity Index; CBC: Complete Blood Count;

VOD: Veno-occlusive Disease; aGVHD: acute graft versus host disease; ICU: Intensive Care Unit

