## 2. Methods

### 2.1 Trial Overview

TRIST is an open-labeled multi-center pilot parallel-arm randomized controlled trial, where participants will be stratified by centre (3 centres) and type of HSCT (either autologous or allogeneic). We will recruit patients over a 2 year period and follow each participant for a minimum of 100 days. Following a screening visit to confirm eligibility, patients will be randomized with subsequent study assessments to occur in concert with routine transplant care on Days +7, +14, +28, +60, +100 (where Day 0 is defined as the 1 ^st ^day of stem cell infusion). TRIST has been funded by a peer reviewed grant by the Canadian Blood Services (R & D Intramural Grants Competition 2010) and registered on the National Institute of Health, Clinicaltrials.gov registry (NCT01237639).

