### 2.6 Withdrawal from study

Participants may withdraw from the study at any time and for any reason, or maybe withdrawn at the treating physician's discretion in the event of intolerance to transfusion assignment, adverse events, or administrative reasons.

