### 2.16 Statistical Analysis

The number of eligible participants will be documented and the proportion of randomized patients noted monthly. Recruitment at each participating centre will be summarized by the number of randomized participants on a monthly basis. Feasibility of data collection will be assessed by the number of missing or erroneous data at each centre and summarized by proportions.

Clinical outcomes will be collected as described above; they will be compared between the 2 groups (liberal and restrictive red cell transfusion strategy). These will include transfusion requirements (number of PRBC units, platelets and plasma), transplant related mortality at 100 days (yes/no), maximum grade of acute graft versus host disease, incidence of acute graft versus host disease at 100 days, veno-occlusive disease, incidence of grade 4 and 5 infections at 100 days, Bearman toxicity scores, incidence of bleeding, incidence of hospital admissions, incidence of ICU admissions and quality of life.

Comparisons of time to failure endpoints will incorporate Kaplan-Meier probability estimates, log rank testing and, when adjustment of covariates is made, use of the Cox proportional hazards model. Binary/categorical endpoints will be compared between treatment groups using logistic regression. The effect of missing data and outliers will be subjected to sensitivity analysis. The results for each of endpoints will be summarized by a significance test and 95 per cent confidence interval. Analysis of secondary endpoints will be considered exploratory and hypothesis generating. Given that multiple comparisons increase the probability of a Type I error, adjustment of individual statistical tests using a more strict cut point (p < 0.01) will be used to facilitate interpretation. All statistical tests quoted will be 2-tailed. Analysis will follow the intention-to-treat principle. Analyses will be conducted using SAS version 9.2 and/or SPSS.

Sub-group analysis will be conducted as follows: The two treatment groups will be compared among recipients of allogeneic or autologous Hematopoietic Stem cell Transplantation. Results will be considered hypothesis-generating.

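### The Table 3 note requires assessments after discharge yet assumes discharged patients had no transplant toxicity, so unascertained outcomes may be recorded as none instead of missing

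*Protocol article*

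**What the plan says.** One sentence beneath Table 3 in section 2.10 carries two statements. The first is an instruction: "Scheduled Assessments will be required even if the patient is discharged". The second is a presumption: "the assumption is that no transplant toxicities have occurred if the patient is discharged". The article does not define which outcomes count as transplant toxicities.

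The schedule and outcome windows around that note are:

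- **Bleeding and infection:** assessed at Days 14, 28 and 100. Section 2.16 lists "incidence of grade 4 and 5 infections at 100 days" among the comparisons.
- **Acute GVHD:** highest grade, recorded once at Day 100. Table 2 states: "The incidence of acute GVHD up to Day 100 will be compared".
- **Bearman toxicity:** assessed at Day 28 and scored through Day 28, with later deaths from earlier toxicity also counted.
- **Veno-occlusive disease (VOD):** assessed at Day 28. The window is 20 days in Table 2 and 21 days in the Table 3 footnote.
- **Mortality:** assessed at Day 100. Transfusions, hospital admissions and ICU admissions are recorded as they occur. Quality of life has its own questionnaires through Day 100.

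Table 3 gives a visit window for outpatients (±5 days) as well as inpatients (±3 days), and section 2.1 undertakes to "follow each participant for a minimum of 100 days". Section 2.11 offers accurate event rates for all the clinical outcomes as a benefit of the pilot. Section 2.16 plans a sensitivity analysis for missing data and judges the feasibility of data collection by the amount of missing or erroneous data at each centre.

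**The concern.** A coordinator completing a form for a discharged patient gets two answers from one sentence: assess the patient, or take it that nothing happened. If the second is followed, an unknown outcome becomes a recorded negative. That is a single-value imputation in the favourable direction, made at the point of data entry.

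Three things are at stake. Recorded event rates would be too low, although estimating them is one reason for running the pilot. An entry of none is not a missing value, so it would not be counted in the feasibility measure, queried under section 2.12, or varied in the sensitivity analysis. And the same outcomes feed the interim safety reports listed in section 2.15.

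**Working it through.** **Is there a figure in the plan to reproduce?** Not on this point. The power of 7.3% in section 2.11 concerns 100-day mortality, which the note cannot alter, and it is not in dispute here.

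**Which outcomes can the note reach?**

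| Outcome | Window | Exposure to the assumption |
|---|---|---|
| Bearman toxicity | through Day 28 | Plain, for discharge before Day 28 |
| VOD | Day 20 (Table 2) or 21 (Table 3) | Plain, for discharge before the window closes |
| Infection, bleeding | to Day 100; no scheduled assessment between Days 28 and 100 | Only if the term includes them |
| Acute GVHD | to Day 100, one recording | Only if the term includes it |
| Death, transfusions, admissions, quality of life | to Day 100 | None |

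The middle rows are open because the document points both ways. Table 3 places bleeding, infection, VOD, Bearman and acute GVHD under one heading of transplant assessments. The Bearman definition in Table 2, however, excludes events attributable to culture-documented infection or bleeding.

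**What would under-recording do?** The document gives neither a discharge time nor the share of events after discharge. Let *m* be the share of patients with an event whose form says none because of the assumption. Then

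observed rate = true rate × (1 − *m*).

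*Equal loss in both arms.* Take true rates of 30% and 20% (assumption, for illustration). N per arm is for 80% power, two-sided α = 0.05, pooled two-proportion test without continuity correction, calculated from the observed rates.

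| *m* (assumed) | Observed rates | Risk difference | Risk ratio | N per arm |
|---|---|---|---|---|
| 0 | 30% vs 20% | 10 points | 0.667 | 294 |
| 10% | 27% vs 18% | 9 points | 0.667 | 337 |
| 25% | 22.5% vs 15% | 7.5 points | 0.667 | 424 |
| 50% | 15% vs 10% | 5 points | 0.667 | 686 |

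The factor (1 − *m*) cancels in the risk ratio: 0.20(1 − *m*) / 0.30(1 − *m*) = 0.667. It does not cancel in the rates or the risk difference. Nor does it cancel in the odds ratio, the natural output of the logistic regression in section 2.16: (0.20/0.80)/(0.30/0.70) = 0.583 at *m* = 0, against (0.10/0.90)/(0.15/0.85) = 0.630 at *m* = 50%.

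*Unequal loss, no true effect.* Take a true rate of 20% in both arms (assumption).

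- *m* = 10% and 20%: 0.20 × 0.90 = 18% against 0.20 × 0.80 = 16%. Spurious difference 2 points, risk ratio 0.89.
- *m* = 20% and 40%: 0.20 × 0.80 = 16% against 0.20 × 0.60 = 12%. Spurious difference 4 points, risk ratio 0.75.

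*No loss.* If every required assessment is done and recorded, *m* = 0 and there is no error.

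**The case against.** The best defence is the first half of the sentence. Assessments are required after discharge, outpatient windows are provided, visits run to Day 100 alongside routine care, and section 2.12 has coordinators check forms against source documents and resolve missing-data queries. On that reading the assumption is loose wording with little effect. Moreover, the primary goal is feasibility, and analyses of secondary endpoints are declared exploratory.

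Much of this stands. A reader might infer that the plan has a settled rule setting post-discharge events to zero; it does not, because zero-filling is one reading of a contradictory note. A reader might also infer that every outcome from Day 28 to Day 100 is biased. The text does not support that: the outcomes most plainly meant close by Day 28, and the main clinical outcome, death from any cause, cannot be set to zero by this note. Nor does the document suggest that discharge timing differs by arm, so open-label treatment alone does not establish a biased comparison.

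The defence does not remove the assumption from the page. A value entered as none raises no missing-data query, and a sensitivity analysis for missing data cannot reach values never coded missing. The pilot's purpose does not excuse it either, because event rates and data completeness are among the things the pilot is meant to deliver.

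**Conclusion.** The point holds as an internal contradiction with a conditional consequence. If the assumption is used to complete forms, Bearman and VOD events after early discharge are under-recorded. Infection, bleeding and acute GVHD to Day 100 join them if the undefined term covers those outcomes. The missing-data count and sensitivity analysis would then look better than they should.

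The size cannot be derived from the document. An equal loss of 10–50% of events (assumption) lowers observed rates by 10–50% in relative terms, shrinks the risk difference in proportion and leaves the risk ratio unchanged. A difference where none exists arises only if discharge timing or post-discharge ascertainment differs by arm.

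Two neighbouring passages may tempt a reader to go further. Section 2.6 allows withdrawal at the treating physician's discretion, but it does not say that follow-up or data collection then ends, so it does not follow that intention-to-treat analysis is out of reach. Section 2.9's view of measurement bias is a separate matter, neither caused nor cured by the Table 3 note. Neither is part of this point.

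**What to change.** 1. Delete the assumption from the Table 3 note and keep the requirement for assessments after discharge.
2. For discharged patients, score Bearman toxicity, VOD, infection, bleeding and acute GVHD from clinic, readmission and laboratory records at the visits already scheduled. Naming these outcomes also removes the undefined term.
3. Where no record was reviewed, code the outcome as missing, not as none.
4. Include those missing values in the sensitivity analysis and the per-centre missing-data count of section 2.16.

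The cost is a change to protocol and case report form wording, modest chart review, and a less favourable but truthful missing-data proportion. Section 4 reports 20 + 1 = 21 patients enrolled of a planned 100, so most of the data can still be collected under the clearer rule.
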